## Abstract

**Background:**

Mental health issues pose a serious concern in the workplace for the huge productivity loss and financial burden associated with it. Unlike the traditional ‘fixing-what-is-wrong’ approach, positive psychology offers a less-stigmatized way to promote mental health. Psychological capital, a concept originated from positive psychology, has been proven effective in improving mental well-being and work performance. However, little evidence exists for its implementation among Asian working population or its cost-benefit for organizations adopting such promotion strategy. The current study is designed to assess the protective effects of a web-based psychology capital intervention among Hong Kong working population on individuals’ mental health and work performance, as well as organizations’ return-on-investment.

**Methods/Design:**

A two-arm randomized controlled trial design will be adopted. Eligible working adults will be randomly allocated to either the intervention group or the waiting-list control group, with 177 participants in each arm. The intervention, which consists of four web-based training sessions, each targeting one of the psychological capital components (hope, efficacy, optimism and resilience), will be implemented over a 4-week period. On-line surveys will assess the participants in each group at baseline, intervention completion, 1 and 3 months after the completion. The primary outcome is individuals’ psychological capital level; secondary outcomes include individuals’ well-being, depressive symptoms, work engagement and productivity. Return-on-investment will be calculated from the employers’ perspective based on productivity gain, savings in medical expenditure, as well as operation and time costs. Analysis will follow the intention-to-treat principle.

**Discussion:**

This is the first experimental study that explores the applicability of psychological capital development among Asian population. Through investigating changes in individuals’ work productivity from absenteeism and presenteeism, this will be one of the few studies that quantify productivity gains from any type of mental health promotion. By demonstrating effectiveness in improving mental well-being and a positive return-on-investment rate, the study may help convince more uptake of similar positive psychology interventions at workplace in Asia and elsewhere.

**Trail Registration:**

Number (assigned by Centre for Clinical Trials, Clinical Trials Registry, The Chinese University of Hong Kong): CUHK_CCT00396. Registration Date: 2014/02/13

## Background

Accounting for 5.45% of global disease burden in 2010, mental disorders have become a significant public health threat and are expected to cause even heavier burden to society in the coming years [1]. The economic loss associated with mental disorders is particularly striking among the working-age adults, as these conditions affect individuals’ work performance, short-term disability, absenteeism, as well as turnover rate [2,3]. These, in turn, affect productivity and business performance. Estimates indicate that mental disorders had cost the business sector $50.7 billion in the United States [4], $14.4 billion in Canada [5] and $14.8 billion in Australia [6] annually. Globally, the cumulative loss of economic output due to mental disorders is estimated to reach $16 trillion in the next 20 years, or 25% of world Gross Domestic Product (GDP) in 2010 [7]. Since 2000, the World Health Organization (WHO) has pointed out that there is a need among employers to recognize mental health issues as a legitimate workplace concern [8].

However, mental disorders are usually associated with stigma and discrimination. Compared with treating the diseases themselves, coping with the stigma is often reported to be more difficult [9]. In the workplace where individuals are supposed to be productive, such stigma can be worse. Employees with depression or other mental disorders may avoid assistance and effective treatment, as a result [10]. Facing this challenge, promoters of workplace mental health have been searching for an alternative more positive approach than the traditional “fixing-what-is-wrong” intervention. The rationale for positive psychology interventions (PPIs) is to nurture the strengths or positive traits of individuals, thereby buffer the negative effects of stressors and improve their mental health status. It represents a far-less-stigmatized approach, therefore, has more potential to be effective as a general strategy for prevention, particularly in the workplace. Indeed, previous studies among both general population [11] and working population [12,13] demonstrated that PPIs are effective in promoting subjective well-being, with an effect size of 0.3 [14].

Based on the principles of positive psychology and organization behavior, Luthans and colleagues further developed the concept of Psychological Capital (PsyCap) [15]. It includes four personal strengths (namely, hope, efficacy, optimism and resilience), which are theoretical based, state-like (measurable and developable) and manageable for work performance improvements [15]. The potential role of PsyCap in promoting mental health in the workplace could be better illustrated through the Conservation of Resources (COR) Theory. Under the COR theory, people seek to obtain, retain, and protect resources; and stress occurs when there is a net loss of resources, the threat of loss, or a lack of resource gain following the investment [16]. At the same time, resource gains could buffer the negative effects of resource loss and create more opportunity for further gains [17].

For employees, workplace adversities are natural circumstances for resource loss, which could then lead to stress; while PsyCap, just like human and social capital, can be considered as another resource that is developable and accumulative. Gaining such resource therefore will have a potential protective effect against future resource loss. Evidence could be found in a cross-sectional study, which reported higher PsyCap level associated with higher psychological well-being over time [18]. This is further confirmed by one meta-analysis, in which a significant positive relationship between PsyCap and desirable employee attitudes, behaviors and performance was reported [19]. However, almost all the studies that explore the relationship between PsyCap and mental health outcomes by now were observational and cross-sectional in nature. Empirical evidence based on more rigorously controlled experimental study is in much need.

### Return-on-investment from employers’ perspective

Given the large stake that employers have in avoiding the cost associated with mental disorders among staff and the potential benefit the improved productivity could bring, it is not surprising that employers, particularly large companies have started investing in programs promoting mental health at workplace [20,21]. The question is whether these programs would have positive return-on-investment (ROI). Only upon proving positive ROI and making the business case can more employers be convinced to do more on this important issue, which could in turn have bigger public health impact. There has been only one previous study that estimated a ROI of 2.7 for PsyCap development [22]. The study, however, was based on a small sample from a single company, without a direct measure of improvement in work performance. The gap left in the literature is yet to be filled.

### Mental health among working population in Hong Kong

Although cross-cultural differences in expressing, interpreting and treating symptoms of mental disorders have long been recognized, studies of psychological interventions have predominantly focused among Caucasians in America and Europe [23]. With more and more Asian countries recognizing the rising burden associated with mental disorders [24], there is an increasing need of culturally competent interventions and studies evaluating their effectiveness in this part of the world. Such need is particularly strong in Hong Kong, where an estimated 14.5- 24.6 percent of citizens have a mental disorder [25]. Specifically for working population, the *2008 Hong Kong Work and Life Balance Survey* showed that the average work week is about 49.6 hours, 25 percent more than the global standard; more than 80 percent of people said that they suffered stress, and 28% reported depression [26]. Given the increasing burden of mental disorders, the WHO suggested that priority should be put on prevention and promotion [27]. However, in Hong Kong, most of the resources remain in treatment, and only a disproportionately small amount is placed on prevention [28].

Like many Asian societies, Confucianism, with collectivism as one of its key traditions [29], is rooted in Hong Kong [30]. Although several experimental studies [31-33] demonstrated that PsyCap was developable, none was targeting Asian population. How would a PsyCap intervention work in promoting mental well-being and producing positive ROI among an Asian population that emphasizes collectivism rather than individualism, such as the working population in Hong Kong? This is the key research question we try to answer with this research protocol.

### Aims of the research

Our study aims to demonstrate the effectiveness and cost-effectiveness of a psychological capital development intervention (named “*Happy@Work”)* for improving the mental well-being among working population in Hong Kong. Through designing the intervention in an on-line platform customized for local business and social environment, we will investigate the processes by which individuals from the eastern culture may adhere to the treatment and develop PsyCap. Our research will also fill some gaps in the current literature by testing hypotheses raised yet lacking evidence, for example, can the intervention benefit depressed individuals more than non-depressed ones? In addition, we will calculate the ROI of this intervention, intended for the business sector to take further actions.

## Methods/Design

### Study design

This study is designed as a two-arm randomized control trial. Upon visiting the intervention website, individuals will complete an initial screening to determine the eligibility. Eligible participants will continue the registration process and the baseline assessment, followed by an automatic randomization process that assigns the eligible participants into one of two groups. The intervention group will receive a 4-week access to *Happy@Work* trainings that develop each of the four PsyCap components. Measurements are scheduled at baseline, directly after the 4-week PsyCap trainings, and at 1 and 3 months follow up. The control group will be on the waiting list for 4 months before they can access the training materials. Figure 1 shows the flow of the study design.

**Figure 1 F1:**
[figure not shown]
**After the screening, eligible participants will continue the registration process, followed by the baseline assessment.** The automatic randomization afterwards will then randomly allocate them into the intervention and the waiting-list control group. The intervention group participants will receive the Happy@Work trainings; while the control group will be on the waiting-list for 4 months. Both groups need to finish post-intervention, 1-month and 3-month follow-up surveys.

This study is registered in the Centre for Clinical Trials, Clinical Trials Registry, the Chinese University of Hong Kong (CUHK_CCT00396). The study protocol, informed consent procedure and survey instruments have been approved by the Joint Chinese University of Hong Kong - New Territories East Cluster (CUHK-NTEC) Clinical Research Ethics Committee (CREC), under the reference number CRE-2014.001.

### Inclusion and exclusion criteria

Participants will be included if they: (1) are above 18 years old; (2) have a full-time job for at least 1 month (to ensure that we can compare work productivity before and after the intervention); (3) have access to the internet and (4) have sufficient knowledge in using computers and understanding traditional Chinese (i.e., the language the intervention program is developed in).

In order to monetize the work productivity changes, we need information such as monthly salary for participants. In this case, individuals who do not receive any monthly salary from current jobs (e.g. voluntary workers) will be excluded. Because of the ethical consideration and potential contaminations, individuals who are currently receiving professional mental health treatment or taking any psychotropic medication will be excluded as well.

### Sample size

Based on the existing evidence from PPIs, we expect to find a standard effect size of 0.3 or larger comparing the intervention group with the control group [14]. To achieve a statistical power of 80%, given a two-sided alpha of 0.05, we need at least 177 participants in each condition, i.e. a sample size of 354 or more.

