### Recruitment of participants

Since the intervention is designed to cater needs among local general working population, recruitment of participants is open to the public. Advertisement about the *Happy@Work* program is put up in relevant local magazines, websites, and other public space. Anyone who meets the eligibility criteria is welcome to participate. Furthermore, to maximize the recruitment efforts and to increase awareness among employers, we will also approach them directly, targeting consent from Human Resources managers to encourage staff to participate. More specifically, we have strategically teamed up with the Employers’ Federation of Hong Kong in the beginning, so that the Federation can recruit participants from its member organizations (mostly companies of large sizes). We will also contact small-medium enterprises associations and conduct workshops for specific companies through professional networks to further promote the program. During recruitment, we will highlight the potential benefits of the program, appealing to different audiences. For employers, we emphasize its effect on increasing morale and productivity, while reducing turn-over and medical cost; for individuals, we highlight the benefit of improving well-being and career development, while managing stress.

High dropout rate is a challenge often faced by web-based studies. We use several strategies and incentives to mitigate this problem: 1) Email reminders will be sent out to remind participants at different stages (e.g. upon availability of each training session) to adhere to the process and complete all trainings and assessments on schedule; 2) Conditioning on finishing all the assessments, an electronic certificate for participation will be awarded to participants who have successfully completed all four training sessions; 3) a HK$50 cash coupon will be offered to the first 500 participants (in either control or intervention group) who complete all the assessments.

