### Outcome assessment

The primary outcome is the level of psychological capital. The secondary outcomes include well-being, depressive symptoms, work engagement and economic cost-benefit (as measured by work productivity, medical expenditure and time cost for using the website). All these measures are self-reported, and will be collected through the *Happy@Work* website. Assessments will be made at the baseline, immediately after individuals finish the 4-week trainings, and at 1 and 3 months follow-up after the completion. All the measurements, except specified, will be assessed in both control and intervention groups.

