### Data analysis

Results will be reported according to the Consolidated Standards of Reporting Trials (CONSORT) statement regarding eHealth [55]. The primary data analysis will follow the intention-to-treat principle and compare the differences in the above outcome measures between the intervention group and the wait-list control group. Because of the potential dropout, missing data is expected. When appropriate, we will use the expectation-maximization (EM) method to impute missing data [56]. In addition, per-protocol analysis will also be conducted.

The two groups will first be described in terms of their baseline characteristics. The primary data analysis will compare the effectiveness of *Happy@Work* in the intervention group with the changes in the control group, based on the differences on PsyCap-24, WEMWS, SWLS, CES-D and UWES. Repeated measures of ANOVA will be used to check the multivariate main effects of intervention (compared with control) and time (pre, post, follow-up), as well as their interaction effect. A two-sided P value of 0.05 or less will be considered as significant. We will compute the standardized effect size (Cohen’s d) as well. Moderator analysis will also be conducted to explore which sub-group/s would benefit more from the intervention, by regressing outcome variables on independent variables like age, gender, education and baseline CES-D scores. Work productivity change will be compared between these two groups as well. SPSS V.18 will be used for the data analysis.

To make the business case for similar type of interventions, return-on-investment of the program will be calculated from the employers’ perspective using the following formula:

ROI = (Gain from investment - Cost of investment)/Cost of the investment;

where, *Gain from investment* = total monetized value of employees’ work productivity gains + savings in employers’ share of medical cost; and

*Cost of investment* = Program designing and operation costs (assuming employers self-fund similar programs) + the monetized time cost (if employees use work time for the program training*).*

Self-reported monthly salary will be used to monetize the work productivity changes and time cost for each individual. All the afore-mentioned items will be the incremental value compared with the control group.

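### 177 per arm is the complete-data sample size with essentially no allowance for loss, yet it is also given as the number allocated in a trial that expects missing data, so 354 randomised do not deliver the stated 80% power

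*Protocol article*

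**What the plan says.** The Sample size section assumes a standardised difference of at least 0.3 between intervention and waiting-list control, 80% power and two-sided alpha 0.05, and concludes: "we need at least 177 participants in each condition, i.e. a sample size of 354 or more". It mentions neither a dropout rate nor an inflation for dropout. The Methods/Design paragraph of the Abstract describes random allocation "with 177 participants in each arm".

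Three other places anticipate loss. Recruitment of participants says "High dropout rate is a challenge often faced by web-based studies" and lists reminders and incentives to limit it. Data analysis says "Because of the potential dropout, missing data is expected" and plans EM imputation where appropriate. Strengths and limitations names a possibly high dropout rate as a limitation that may remain despite those measures.

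On the effect size, Sample size cites reference 14. The Background describes the finding of that reference as follows: "PPIs are effective in promoting subjective well-being, with an effect size of 0.3". Outcome assessment states "The primary outcome is the level of psychological capital" and lists well-being among the secondary outcomes. The article quotes no effect size for psychological capital.

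**The concern.** A power calculation of this kind counts participants whose outcome is observed. If the same number is used as the number randomised, and some outcomes will be missing, the trial has less power than it states. The 80% figure is the only justification given for the sample size, so a null result on PsyCap-24 would be read as coming from a trial with 80% power at 0.3 when the actual power may have been clearly lower.

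The second strand is one of disclosure. A reader of the Sample size section alone would take 0.3 to be evidence about the primary outcome, whereas the Background shows that it comes from another outcome.

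**Working it through.** **Inputs from the protocol article.** Standardised difference d = 0.3 (so SD = 1), power 80%, two-sided alpha 0.05, equal arms (Sample size); 177 allocated per arm (Abstract).

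**Inputs not in the documents, assumed here.** Loss of 10 to 50% with an observed primary outcome missing; baseline-to-outcome correlation of 0.5 or 0.6.

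**Step 1: reproduce 177.** Normal approximation: n per arm = 2 × (1.960 + 0.842)² / 0.3² = 174.4, so 175. The t-based calculation gives 175.4, so 176. Power by the t distribution is 80.4% at 177 per arm, 80.1% at 176 and 79.9% at 175. The stated figure is therefore reproduced to within one or two participants, and it contains no inflation. A one-sided test would need 138, which does not match.

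**Step 2: power if 177 per arm are randomised.** Observed per arm = 177 × (1 − loss). Power is t-based at d = 0.3. To keep 177 observed, the number to randomise is 177 / (1 − loss), rounded up.

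| Assumed loss | Observed per arm | Power | Per arm (total) to keep 177 observed |
|---|---|---|---|
| 10% | 159.3 | 76% | 197 (394) |
| 20% | 141.6 | 71% | 222 (444) |
| 30% | 123.9 | 65% | 253 (506) |
| 40% | 106.2 | 59% | 295 (590) |
| 50% | 88.5 | 51% | 354 (708) |

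The difference detectable with 80% power rises from 0.30 with no loss to 0.33, 0.36 and 0.39 at 20, 30 and 40% loss.

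**Step 3: could baseline data make up the loss?** The Data analysis section plans repeated-measures ANOVA with group, time and their interaction; it does not plan ANCOVA. For a simple pre-post contrast, the interaction is a comparison of change scores, with effective difference d / √(2(1 − ρ)). ANCOVA would have d / √(1 − ρ²). At ρ = 0.6 these are 0.3 / √0.8 = 0.335 and 0.3 / √0.64 = 0.375. At ρ = 0.5 the change-score divisor is √1 = 1, so nothing is gained.

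| Assumed loss | No baseline | Change score, ρ = 0.5 | Change score, ρ = 0.6 | ANCOVA, ρ = 0.6 (not planned) |
|---|---|---|---|---|
| 20% | 71% | 71% | 80% | 88% |
| 30% | 65% | 65% | 75% | 84% |
| 40% | 59% | 59% | 68% | 78% |

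Other contrasts over the four visits would give other values, and the article does not single one out.

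**Step 4: source of the 0.3.** Sample size and Background cite the same reference. The Background ties its 0.3 to subjective well-being, and Outcome assessment makes psychological capital primary. With 177 per arm and no loss, power (normal approximation) is 47% at d = 0.20, 65% at 0.25 and 96% at 0.40, so the assumption matters in both directions.

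**The case against.** The strongest reply is that the Sample size section states a floor, both per arm and in total. Recruitment is open to the public without a stated cap, and cash coupons are offered to the first 500 participants who complete every assessment. That suggests that more than 354 may have been envisaged, and the 177 allocated per arm appears only in the Abstract, which is a summary. This softens the point but does not remove it. A coupon limit is not a recruitment target, no larger target or dropout allowance is stated anywhere, and the Sample size section presents 354 as enough for 80% power.

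A second reply is that intention-to-treat analysis with EM imputation keeps everyone in the analysis. It does, but imputation does not restore the information in outcomes that were never observed.

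A third is that repeated measurement recovers power. It may, depending on the contrast and the correlation, but the Sample size section makes no such argument and gives no correlation. A reader might infer that a planned baseline-adjusted analysis already covers the loss; the Data analysis section plans no such analysis.

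Three stronger readings also go too far. A reader might infer that 80% power fails with any dropout at all, but one loss per arm is covered. A reader might infer that heavy dropout is forecast, but the article gives no rate and speaks only of a possibly high one. And a reader might infer that 0.3 is too optimistic for PsyCap-24. Nothing shows this; the effect could be larger or smaller, and the section does disclose that its evidence comes from positive psychology interventions as a class.

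**Conclusion.** The point stands as a missing allowance, not as an arithmetic error: 177 is correct as a complete-data number. On the protocol's own unadjusted two-sample basis, 354 randomised do not deliver 80% power at 0.3 once more than about one participant per arm is lost. The size of the shortfall rests on assumed loss: about 9 percentage points below 80% at 20% loss (71%), 15 at 30% (65%) and 21 at 40% (59%). An analysis that uses baseline could reduce or close this gap, but only conditionally on the contrast chosen and on a correlation that the documents do not give. The effect-size strand is a matter of disclosure only.

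**What to change.** Reword the Sample size section along these lines: 177 participants per arm with an observed primary outcome are required for 80% power at d = 0.3; if 354 are randomised and 20, 30 or 40% are lost, power for the unadjusted comparison is 71, 65 or 59%. The sponsor should replace this range with its own stated range if it has one. Align the Abstract, so that 177 is not both the number allocated and the number required with outcomes.

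If a gain from baseline data is quoted, label it as conditional on the analysis and on an assumed correlation, show a range of correlations, and do not call ANCOVA planned unless it is adopted in the Data analysis section.

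Add one sentence stating that 0.3 is the cited effect of positive psychology interventions on subjective well-being and is assumed for PsyCap-24.

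The cost is a rewritten paragraph and a less favourable quoted power. The restatement requires no extra enrolment. Keeping 80% power by inflation would, for example 444 randomised at 20% loss or 506 at 30%, but that is a separate decision.
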